### Economic evaluation

For the economic evaluation, missing cost and effect data will be imputed using multiple imputation according to the Multivariate Imputation by Chained Equations (MICE) algorithm developed by van Buuren using predictive mean matching and fully conditional specification [55]. The number of imputed datasets will be increased until the fraction of missing information is below 5% [56]. The imputed datasets will be analysed separately as described below and subsequently pooled using Rubin’s rules.

The effect measures that will be taken into account in the cost-effectiveness are QALYs, and changes in the VAS scores of the geriatric giant symptoms. For effects and costs, linear multilevel regression models will be estimated. Clustering at the level of GP practice will be included in these multilevel models. Incremental cost-effectiveness ratios (ICERs) will be calculated by dividing the difference in mean total costs between the treatment and control groups by the difference in mean effects between the groups. Costs generally have a highly skewed distribution; therefore, bootstrapping with 5,000 replications will be used to estimate bias-corrected and accelerated confidence intervals around cost differences [57]. To account for the clustering of data, bootstrap replications will be stratified for practice [58]. The uncertainty surrounding the ICERs which will be graphically presented on cost-effectiveness planes. Cost-effectiveness acceptability curves and net monetary benefits will also be calculated. Cost-effectiveness acceptability curves show the probability that the medication review programme is cost-effective in comparison with usual care for a range of different ceiling ratios thereby showing decision uncertainty.

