### Sample size

The size of the study groups is based on the difference in change over 6 months between the intervention and control group of the EQ-5D VAS score (score range 0–100). A difference of 7.4 in the EQ-5D VAS is considered as a clinically relevant difference [54]. The average score among persons with osteoarthritis, a comparable group, is 64.8 (standard deviation 26.5). To establish a difference of 7.4 points as statistically significant with alpha = 0.05 and beta = 0.20, a group size of 225 is sufficient, taking the clustered design into account. To adjust for loss to follow up of 10% we will include 500 patients.

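### The number of imputations is tied to the fraction of missing information, a quantity that adding imputations does not drive below 5%

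*Protocol article*

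**What the plan says.** The Economic evaluation section of the Protocol article says that "missing cost and effect data will be imputed using multiple imputation", by chained equations "using predictive mean matching and fully conditional specification". It then sets the number of imputations by a stopping rule: "The number of imputed datasets will be increased until the fraction of missing information is below 5" per cent. Pooling is also fixed: "The imputed datasets will be analysed separately as described below and subsequently pooled using Rubin’s rules". The section gives no starting or maximum number of imputations and mentions neither loss of efficiency nor Monte Carlo error. The only missing-data figure in the article is in Sample size: "To adjust for loss to follow up of 10% we will include 500 patients".

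**The concern.** The rule treats the FMI as something that more imputations reduce. It is mainly a property of the data and the imputation model. More imputations estimate it more precisely and remove a small finite-M excess, but do not push it below its limit. What falls with M is the loss of efficiency relative to infinitely many imputations, roughly FMI/M.

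The issue is whether the stated rule can deliver a number of imputations. For an outcome whose limiting FMI is at or above the threshold, the analyst either goes on without end, picks M outside the rule, or stops when the estimate happens to dip. For an outcome with a limit below the threshold, the rule is satisfied without regard to simulation error in the pooled result.

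**Working it through.** **Inputs.** From the article: the 5% threshold and pooling by Rubin's rules (Economic evaluation), 10% loss to follow-up (Sample size), and QALYs by linear interpolation over baseline, 3 and 6 months (Primary outcome measures). Assumed, because the article does not give them: the limiting FMI, the variance explained by predictors (R²), the between-visit correlation, and any missingness above 10%.

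**1. FMI as M grows.** With within-imputation variance W and between-imputation variance B:

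- r = (1 + 1/M)B/W
- df = (M − 1)(1 + 1/r)²
- FMI = (r + 2/(df + 3))/(r + 1)

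As M increases this tends to B/(B + W). For B = 0.10, W = 0.90 and M = 5: r = 1.2 × 0.10/0.90 = 0.1333, df = 4 × 8.5² = 289, and FMI = (0.1333 + 2/292)/1.1333 = 12.4%.

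| Limiting FMI | M = 5 | M = 20 | M = 100 | M = 1,000 |
|---|---|---|---|---|
| 2% | 2.4% | 2.1% | 2.0% | 2.0% |
| 10% | 12.4% | 10.6% | 10.1% | 10.0% |
| 20% | 25.0% | 21.2% | 20.2% | 20.0% |
| 30% | 37.5% | 31.7% | 30.3% | 30.0% |

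These values put the expected B into the formula. Averaging simulated estimates instead gives about 11.8%, 10.5%, 10.1% and 10.0% in the 10% row. Each row levels off at its own limit. By contrast, FMI/M in the 10% row is 2%, 0.5%, 0.1% and 0.01%.

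**2. Is the limit likely to exceed 5%?** For a mean with a proportion d missing, approximately FMI = 1 − 1/v, with v = 1 + [d/(1 − d)](1 − R²).

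| d | R² = 0 | 0.3 | 0.5 | 0.6 |
|---|---|---|---|---|
| 10% | 10.0% | 7.2% | 5.3% | 4.3% |
| 20% (assumed) | 20.0% | 14.9% | 11.1% | 9.1% |

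FMI = 5% means v − 1 = 0.05/0.95 = 0.0526. At d = 10%, 1 − R² = 0.0526 × 9 = 0.474, so R² must exceed about 0.53. At d = 20%, 1 − R² = 0.0526 × 4 = 0.211, so R² must exceed about 0.79.

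**3. Outcomes differ.** An interpolated QALY is proportional to u0 + 2u3 + u6. With equal SDs and a common correlation ρ, its variance is 6 + 10ρ. Take complete baselines and 10% loss.

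- Only month 6 missing: the unexplained variance is 1 − 2ρ²/(1 + ρ). For ρ = 0.4 this is 0.771 out of 10, so FMI = 0.9%. For ρ = 0.7 it is 0.424 out of 13, so FMI = 0.4%.
- Months 3 and 6 missing: the unexplained variance is 5(1 − ρ²) + 4ρ(1 − ρ). For ρ = 0.4 this is 5.16 out of 10, so FMI = 5.4%. For ρ = 0.7 it is 3.39 out of 13, so FMI = 2.8%.
- Change in a symptom VAS score predicted from baseline alone: the unexplained share is (1 − ρ²)/[2(1 − ρ)] = (1 + ρ)/2. This is 0.70 to 0.85, so FMI is about 7% to 9%.

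**4. Stopping by chance.** With a limiting FMI of 10%, about 18% of single estimates fall below 5% at M = 5, 2% at M = 20 and none at M = 100. Applied sequentially up to M = 200 (4,000 simulated runs), the rule stops at some point in 27% of runs if checked from M = 5 and in 2.6% if checked from M = 20. With a limit of 20%, the figures are 5.4% and 0.03%.

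To size the effect, treat the FMI as the between-imputation share. Stopping at an estimate of 5% when the truth is 10% gives a variance ratio of 0.90/0.95 = 0.947. The standard error is then √0.947 = 0.973 of its proper size, about 3% too small.

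**5. The threshold applied to FMI/M.** The smallest M with FMI/M below 5% is 3, 5, 7 and 9 for an FMI of 10%, 20%, 30% and 40%. Setting M at 100 times the FMI gives 10, 20, 30 and 40.

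**The case against.** The strongest reply is that the sentence is recognisable shorthand for loss of efficiency, written in a condensed article, and that a competent analyst would choose an adequate M. That is probably what was meant. But the text names the FMI, nothing else in the article corrects it, and the two readings give different instructions: 3 to 9 imputations in step 5 against no stopping point. This is a rule stated wrongly, not a detail left to a fuller document. The source cited for the rule was not available, so the sentence is taken as it stands.

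A reader might infer that the rule can never be carried out. The documents do not support that. At 10% loss and plausible correlations, the limiting FMI for interpolated QALYs is mostly below 5%, so the rule would stop. Prescribed-medication data come from pharmacy records, which limits missing cost data, and missingness above 10% is an assumption.

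Nor should the harm be pressed too far. A rule that keeps running adds imputations and so reduces Monte Carlo error. Stopping by chance is mainly a small-M problem. The FMI does not reveal the direction of the treatment difference, so the article gives no ground for suspecting that M would be steered by results. These points limit the consequence but do not make the criterion right.

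**Conclusion.** The stopping rule names the wrong quantity. For any cost or effect difference with a limiting FMI of 5% or more, it never stops or stops on a chance low estimate at small M. Where the limit is below 5%, it is met whatever the Monte Carlo error. Which case applies to which outcome rests on assumed R² and correlations: symptom VAS changes (about 7% to 9%), and possibly costs, fall in the first group, and interpolated QALYs (about 0.4% to 5.4%) mostly in the second.

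The size is modest. An early chance stop at a 10% limit would shrink a standard error by about 3%. The main damage is that the plan does not determine M where it matters. The error is confined to the economic evaluation, since the Statistical analyses section ties no imputation to the clinical effect analyses. It is still worth correcting, because cost-effectiveness is part of the trial's stated aim.

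**What to change.** Replace the sentence with one criterion that falls with M. Either: 'The number of imputations M will be increased until the loss of efficiency (FMI/M) is below 5% for every cost and effect difference.' Or, more strictly and instead of it: 'M will be at least 100 times the largest FMI among the cost and effect differences.' The two should not be combined, because the second already holds FMI/M to 1% or less and the first would never bind. The stricter form also avoids judging the FMI from only a handful of imputations.

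The cost is one sentence and slightly more computing time, since each added dataset carries its own 5,000 bootstrap replications. Unlike the present wording, either form ends at a finite M.

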**Methods:**

A cluster randomised controlled trial will be performed in 20 Dutch general practices including 500 patients. Patients of 65 years and older are eligible if they newly present with pre-specified geriatric symptoms in general practice and chronic use of at least one prescribed drug. GP practices will be stratified by practice size and randomly allocated to control (n = 10) or intervention group (n = 10). The intervention consists of CMRs which will be facilitated and prepared by an expert team consisting of a GP and a pharmacist. Primary outcome measures are patient’s quality of life and the presence of self-reported geriatric symptoms during a follow-up period of 6 months. Secondary outcomes are costs of healthcare utilisation, feasibility, number of drug related problems, medication adherence and satisfaction with medication.

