### Study design

A cluster randomised clinical trial will be performed in 20 general practices including 500 patients (see Figure 1). Allocation of the intervention and control condition will be carried out randomly at practice level. Eligible patients will be invited to participate in the study and the medication of the patients listed in the intervention practices will be reviewed. Patients listed in the control practices will receive usual care, with no systematic attention for their medication. The effects of this intervention will be assessed after a follow-up period of 6 months. The rationale to use a cluster design at practice level is to prevent contamination of structural attention to CMR activities within the GP practice.

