### Randomisation

Randomisation will be performed by a statistician blinded to characteristics of the practices using a computer generated list of random numbers. The practices are stratified by practice size (two strata), to ensure equally sized groups. Before patients are recruited, participating practices will be randomly allocated to the intervention, or control condition. Patients will be allocated to either one of the treatment conditions, based on the practice where they are listed. Blinding of patients, GPs and practice nurses to treatment allocation is not possible due to the nature of the intervention.

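### The bootstrap for cost differences is stratified by practice, so it leaves out between-practice variation and gives intervals that are too narrow unless practices hardly differ in cost

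*Protocol article*

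**What the plan says.** The article's Study design section makes the practice the unit of allocation: "Allocation of the intervention and control condition will be carried out randomly at practice level". It plans 20 practices and 500 patients, and the abstract gives ten practices per arm. The design strata are practice-size groups, not practices: "The practices are stratified by practice size (two strata), to ensure equally sized groups" (Randomisation).

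Under Economic evaluation, costs and effects are modelled with linear multilevel regression, and "Clustering at the level of GP practice will be included in these multilevel models". The uncertainty of the cost comparison, however, comes from resampling: "bootstrapping with 5,000 replications will be used to estimate bias-corrected and accelerated confidence intervals around cost differences". The next sentence fixes how replicates are drawn: "To account for the clustering of data, bootstrap replications will be stratified for practice". The same paragraph goes on to cost-effectiveness planes, acceptability curves and net monetary benefits. It mentions no resampling of practices, no two-stage bootstrap and no correction for a small number of clusters.

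**The concern.** A stratified bootstrap keeps every stratum in every replicate and redraws only the units inside it. That suits strata fixed by design. Here practice is the unit that was randomised and is meant to be generalised from, so practice-to-practice differences in mean cost belong in the error of the arm difference. With practice as the stratum, the replicates vary only through patients within practices. The rule removes the component that it is meant to account for.

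Fitting a multilevel model in each replicate does not repair this. Bias-corrected and accelerated (BCa) limits are adjusted quantiles of the replicate estimates, and the model's own standard error does not enter them. Rubin's rules add variance between imputations, not the missing variance between practices.

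At stake is how certain the cost comparison appears. Acceptability curves exist to show decision uncertainty, and the Discussion makes support for nationwide implementation conditional on proven cost-effectiveness.

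**Working it through.** **Inputs.** From the article: 20 practices, 10 per arm, 500 patients (500/20 = 25 per practice; 22.5 after 10% loss); difference 7.4, SD 26.5, alpha 0.05, power 0.80, 225 per group. Assumed: a two-sided test, and an ICC for costs between 0 and 0.10, because none is given.

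**The plan's own figure.** The article states no interval width or coverage. The related figure that can be reproduced is the sample size.
- Without clustering: 2 × (1.96 + 0.84)² × (26.5/7.4)² ≈ 201.3 per group.
- Implied design effect: 225/201.3 = 1.118.
- Implied ICC at 22.5 per practice: 0.118/21.5 ≈ 0.0055. Rounding 201.3 up to 202 gives 0.0053.
- Loss of 10%: 225/0.90 = 250 per group, 500 in total, as stated.

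This ICC belongs to the EQ-5D VAS. It says nothing direct about costs.

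**Standard error ratio.** With m patients in each of k practices per arm, and total variance set to 1:
- true variance of an arm mean: [1 + (m − 1) × ICC]/(k × m);
- variance seen by the stratified bootstrap: (1 − ICC)/(k × m), times (m − 1)/m because each practice is resampled from its own m patients;
- ratio of standard errors without that last factor: √{(1 − ICC)/[1 + (m − 1) × ICC]}.

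Example at m = 25, ICC 0.05: √(0.95/2.20) = 0.66. With the last factor, 0.657 × √(24/25) = 0.644, and normal-theory coverage is 2Φ(1.96 × 0.644) − 1 = 79.3%.

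| ICC | SE ratio | SE ratio with (m − 1)/m | Coverage of nominal 95% (from previous column) |
|---|---|---|---|
| 0.0055 | 0.94 | 0.92 | 92.8% |
| 0.02 | 0.81 | 0.80 | 88.2% |
| 0.05 | 0.66 | 0.64 | 79.3% |
| 0.10 | 0.51 | 0.50 | 67.7% |

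**Simulation with the model refitted.** Ten practices per arm, 13 to 32 patients each, lognormal costs within practice, a random-intercept model refitted in every replicate; 800 trials per ICC, 600 replicates each.

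| ICC | True SE (SD units) | Stratified 95% width (percentile) | Stratified BCa coverage | Stratified percentile coverage | Whole-practice percentile coverage, uncorrected | Multilevel model, t on 18 df |
|---|---|---|---|---|---|---|
| 0 | 0.092 | 0.359 | 92.5% | 94.8% | 93.8% | 97.8% |
| 0.005 | 0.102 | 0.361 | 89.2% | 90.9% | 91.0% | 95.9% |
| 0.02 | 0.116 | 0.352 | 83.8% | 87.1% | 91.1% | 94.8% |
| 0.05 | 0.140 | 0.351 | 78.4% | 78.8% | 90.8% | 93.4% |
| 0.10 | 0.168 | 0.342 | 65.0% | 65.8% | 91.2% | 95.2% |

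The true standard error rises by about 80% from top to bottom, while the stratified interval does not widen at all. Skewed costs lower the BCa figures somewhat below the formula.

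**Plain whole-practice resampling.** Drawing 10 practices from 10 shrinks the variance by 9/10 and leaves 18 df, so with equal practices the coverage is P(|t₁₈| < 1.96 × √0.9) = 92.1% at any ICC. That is slightly below the stratified 92.8% at ICC 0.0055. The stratified scheme falls to 92.1% at an ICC of about 0.008 and is worse beyond it.

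**The case against.** Four points on the other side have weight.

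- **Size at the only ICC that can be derived.** At 0.0055 the loss is modest, and uncorrected whole-practice resampling does no better. Part of the shortfall is ordinary bootstrap error: stratified BCa coverage is already 92.5% at ICC 0. This stands, and it is why a correction must be part of the fix. It does not clear the rule, because that ICC is not for costs, and by 0.02 the stratified scheme is clearly worse.
- **Scope.** A reader might infer that all cost-effectiveness uncertainty is understated. The article ties the bootstrap explicitly only to cost differences. That planes and curves use the same replicates is the natural reading, but it is not stated. Net monetary benefits are to be calculated, with no mention of intervals. How the bootstrap combines with multiple imputation is also left open.
- **Importance.** Costs are a secondary outcome. Quality of life and geriatric symptoms are analysed with multilevel models that take clustering at GP level into account. A reader might infer that the trial's clinical conclusions are at risk; nothing in the documents supports that.
- **Wording.** The sentence cites reference [58], which is not at hand, and its stated aim is to respect clustering. The authors may have meant that practices are resampled. In that case the error is in the wording, but the sentence as printed instructs something else.

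It could also be said that an article leaves detail to a fuller plan. Here, though, the article fixes a specific resampling rule, and that rule does not do what it is said to do.

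**Conclusion.** The point holds within limits. As written, the rule omits between-practice variance, so the BCa intervals for cost differences are too narrow unless the ICC for costs is near zero. Planes and acceptability curves share the fault if they come from the same replicates. With 25 patients per practice the bootstrap standard error is about 0.94, 0.81, 0.66 and 0.51 of the true one at ICC 0.0055, 0.02, 0.05 and 0.10, with coverage of about 92–93%, 86–88%, 76–79% and 66–69%. Skewed costs with BCa limits can fall a few points lower.

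This rests on the ordinary meaning of a stratified bootstrap and on an assumed ICC range. A reader might infer that the intervals will be about half their proper width; that is so only near ICC 0.10, and nothing in the article shows that costs cluster so strongly. Model-based multilevel estimates and the primary clinical analyses are unaffected.

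**What to change.** Replace the sentence with: *Bootstrap replicates resample whole practices with replacement within arm and practice-size stratum, keep all patients of each drawn practice and refit the multilevel model.*

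Make a small-sample correction part of the rule. Either of these would serve:
- a two-stage bootstrap (practices, then patients) with shrinkage correction; or
- rescaling each replicate's deviation from the estimate, by √(10/9) = 1.05 when drawing from 10 practices per arm, with t limits on about 18 df. The rescaled replicates can also feed the planes and curves.

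In either case, check the result against the multilevel model interval. Keeping the size strata makes the correction matter more. If each arm had five practices per stratum (an assumption; the article does not give the split), the factor would be √(5/4) = 1.12 with 16 df, and uncorrected coverage would be P(|t₁₆| < 1.96 × √0.8) = 90.1%.

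State whether planes and acceptability curves use the same replicates. If reference [58] already describes resampling of practices, correct the sentence to say so.

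The cost is one sentence and a few lines of code, with no new data. The downside is wider, less favourable cost-effectiveness intervals.

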## Discussion

This study is expected to add evidence on the effectiveness and cost-effectiveness of an optimally facilitated, prepared and structured CMR in comparison with usual care in older patients presenting with a geriatric giant to their GP.

Geriatric giants are highly prevalent among older people and represent a major cause of impaired quality of life. Optimising the patient’s medication in addition to treating these geriatric problems or delaying their worsening by treatment, is expected to have a positive additional impact on the patient’s perceived health. Moreover, optimising drug use will also improve the effectiveness of drug treatment, prevent adverse drug reactions and potentially harmful drug interactions, and consequently hospital admissions or even death.

For healthcare professionals, handling DRPs in older people is a challenge. The burden of aging on the healthcare sector, care efficiency is an important issue.

The streamlining of the process, the experienced expert teams and minimising the contact moments with the patients due to the written questionnaire as proposed in this study increases the feasibility that CMRs can be implemented successfully in usual care. In practice, after this study, expert teams could be implemented in a GP cooperation or another regional care settings in which pharmacists and GPs should be trained and form expert groups.

The strength of this study is that it will be conducted in daily clinical practice and will resemble daily clinical practice as much as possible. This improves the possibilities to implement CMRs in the primary care setting.

The most important innovations compared to previous programs are:The CMR will not focus primarily on polypharmacy patients, instead the selection of older patients is based on episodes related to a geriatric giant;The CMR is prepared by a trained expert team consisting of an external GP and an external pharmacist who formulate a pharmacotherapeutic treatment plan for the patient’s GP;The coordination of the CMR at the primary care level is performed by a case manager, usually the practice nurse or assistant;The number of contacts with the patient is reduced by assessing the patient’s perspective by a written questionnaire instead of a home visit.

Quality of life is the primary outcome measure. This may not be sensitive enough to capture the changes induced by the intervention. However, we have chosen to use generic health measures as primary outcome measures because we include patients in this study that might have a variety of geriatric symptoms with a heterogeneous treatment effect. Also we think that in this population quality of life is the most important outcome.

In addition, the study is not blinded and there is a possibility of contamination between the intervention and control group. We counter possible contamination between treatments groups by using a cluster randomised controlled design. That way, caregivers cannot unintentionally apply aspects of the Opti-Med study into their usual care for patients. Patients in the control condition also fill out the screening questionnaire on actual drug use and medication related problems, this is needed for the study, but could underestimate the effectiveness of Opti-Med by increasing awareness of possible drug related problems in these control participants. Furthermore, we suppose that current activities on older people care and possible future pharmacist’s polypharmacy projects are minimally interfering with the study. This assumption about possible contamination will be checked during the process analysis.

Implementation of structured CMR and monitoring will raise the awareness about the importance of optimising medication use in general, and especially in older patients among healthcare professionals. In this study, we will evaluate a form of a structured CMR that can easily be implemented in a GP cooperation or care group. If the CMR is shown (cost-) effective and feasible it could also be extrapolated to other groups of patients in the future in whom inappropriate medication use is suspected as well. If proven cost-effective, this will support the nationwide implementation of this structured approach. The first results of the study will be expected at the end of 2015.

